#### Secondary clinical outcomes

VAS at visit 11, SPADI, ROM, VAS while sleeping, questionnaire of blood-stasis pattern identification, and the number of used bands on visits 11 and 12 (secondary follow-up, fourth week from visit 1 with + 6-day window) will be analysed by the same method as in the primary effectiveness evaluation. For analysing the difference of measurement value between before and after treatment in each group, Student paired *t* test or Wilcoxon signed-rank test will be adapted for effectiveness evaluation variables. To test the difference related to variations of VAS per visit, repeated measures analysis of variance will be conducted, and the adjustment method of multi-comparison will be Dunnett’s procedure. In addition, the subgroups will be analysed depending on the pain severity or post-operation stage.

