## Methods

### Design

This is a randomised, controlled, parallel-designed, exploratory clinical trial. It is an open-label study that will be conducted at DongShin University Gwangju Oriental Hospital, Korea.

Thirty participants who voluntarily submit written informed consent will be randomly allocated to either the intervention group or the control group if the participant is deemed eligible to enter the clinical trial. Both groups of participants will receive ICT therapy because of ethical issues. The intervention group participants will additionally receive 10 sessions of Chimsband therapy over a period of 2 weeks (+ 6-day window), while the control group participants will not receive band therapy. After intervention, both groups will be evaluated at week 4 from visit 1 (+ 6-day window), and the clinical trial will end after the follow-up assessment on each variable at week 4 from visit 1(Fig. 2).

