#### Interferential current therapy (ICT)

The physical therapist will carry out ICT to all participants one time per visit (visit 1 to 10), taking into consideration patients’ shoulder and pain status. The ICT instrument will be the IN-2200 from the Youngin-Medical Corporation, the transportation frequency will be 3750 to 4000 Hz, and the interferential frequency will be 0 to 250 Hz, set to the automatically changed mode. A four-pad electrode will be arranged in a crisscross pattern on the patients’ area of pain. The current strength for therapy will be set at the level of patient tolerance. Strength will be printed in interrupt mode, and adaption time will be 20 min. For the treatment group, the physician will perform physical therapy after removing the Chimsband, and new Chimsband will be attached to the patient’s shoulder when the physical therapy ends.

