### Secondary clinical outcomes

The secondary outcomes will be pain VAS at visit 12, Shoulder Pain and Disability Index (SPADI), range of motion (ROM), shoulder pain VAS while sleeping, blood stasis pattern identification questionnaire, and number of bands used per patients on each visit. All questionnaires will be presented in Korean.

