#### Primary clinical outcomes

Mean VAS variation difference between visit 1 and 11 will be tested by the following hypothesis.

Null-hypothesis (H0): There is no difference in the mean VAS variation between before and after treatment in each group.

Alternative hypothesis (H1): There is a difference between the mean VAS variation before and after treatment in each group.

Mixed-effect Model Repeated Measures (MMRM) will be adapted for fixed factors, namely treatment groups and visiting time, while random factors will be the participants in the trial.

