#### Missing data

This study adopts the MMRM to analyse variations of evaluation parameters for the validity between groups. MMRM considers the missing values by maximum likelihood, not requiring any method of imputing missing values. Conversely, to reduce data loss, the missing values shall be substituted for the Last Observation Carried Forward method in case of adopting the Student paired *t* test (or Wilcoxon signed-rank test) to compare the pre- and post-treatment measurements in groups. Additionally, the Last Observation Carried Forward method shall replace the missing values in case if adopting the repeated measures ANOVA.

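### The number of bands used is put through the between-group MMRM, although the control arm receives no bands by design, so the contrast says nothing about benefit on any reading

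*Protocol article*

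**What the plan says.** The analysis section on secondary outcomes ends its list of variables with "the number of used bands on visits 11 and 12" and says that the list "will be analysed by the same method as in the primary effectiveness evaluation". The primary method is given just before it: "Mixed-effect Model Repeated Measures (MMRM) will be adapted for fixed factors, namely treatment groups and visiting time", with participants as the random factor. The Missing data section states what the model is for: "This study adopts the MMRM to analyse variations of evaluation parameters for the validity between groups".

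On the intervention, the Design section says that Chimsband goes to the intervention group, "while the control group participants will not receive band therapy". The Interventions section likewise gives the control group ICT alone. The Intervention group section sets 10 sessions over 2 weeks. The ICT section places ICT at visits 1 to 10, with a new band put on after each session. The Primary clinical outcomes section under Methods dates visit 11 from the last band attachment or ICT, and the Abstract puts both follow-up visits after the last session.

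On the variable itself, the outcome list under Methods has "number of bands used per patients on each visit". The Number of bands used section and the Abstract also define it as a count at each visit.

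**The concern.** A group comparison is informative only if the variable could take different values in either arm for reasons other than the allocation. The band count cannot: it is fixed at zero in one arm by protocol. The visits attached to it are also follow-up visits, at which no band is due in either arm, and there is no pre-treatment value from which to form a change.

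If the text is followed, the statistician either meets a model that cannot be estimated or obtains a very small p value for a secondary clinical outcome that only confirms who was given bands. The useful information, namely how many bands were applied per session and how that number moved over the course, is not what the planned analysis delivers.

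**Working it through.** **The only stated figure nearby.** The Sample size section goes from 12 to 15 per group for 20% dropout: 12 / (1 − 0.20) = 15. It reproduces. The 12 is a pilot-study rule of thumb, and the point here does not depend on it.

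**Inputs from the protocol article.**
- Control arm: 0 bands at every visit (Design; Interventions).
- Intervention arm: bands attached at 10 sessions, visits 1 to 10 (Intervention group; ICT).
- Visits 11 and 12: assessments after the last attachment (Abstract; Primary clinical outcomes under Methods).
- Method: MMRM with group and visit as fixed factors, participant as random factor. The primary hypothesis concerns change from visit 1 to visit 11.
- Two-sided 5% level.

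**Assumption.** The article gives no expected band count. I take an intervention mean m of 5 to 15 with SD s of 1 to 4.

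**Reading A: raw counts at visits 11 and 12.** The design implies 0 in both arms. With all values zero, the variance is 0, and a two-sample t test returns no value (0/0). A mixed model with group, visit and their interaction on 30 participants × 2 visits = 60 zeros did not converge: residual variance 0, no standard errors. There is no estimable contrast.

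**Reading B: change from visit 1, as in the primary analysis.** Visit 1 is the first treatment session, so an intervention participant has c bands at visit 1 and 0 at follow-up: change = 0 − c = −c. A control participant has 0 − 0 = 0. The group difference in mean change is −m. This can be estimated, because c varies between participants, but it records only that band application has ended.

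**Reading C: counts at the treatment visits.** Intervention mean m, control mean 0, difference m.

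For one visit, B and C have the same test statistic apart from sign. With n per arm and zero variance in the control arm:
- pooled variance = (s² + 0) / 2
- standard error = √[(s² / 2) × (2 / n)] = s / √n
- |t| = m√n / s on 2n − 2 degrees of freedom

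With n = 12 (√12 = 3.46) there are 22 degrees of freedom, and the two-sided 5% critical value is 2.07.

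| Assumed mean m | Assumed SD s | \|t\| at those values | Rejections in 2000 simulated trials (t test) |
|---|---|---|---|
| 5 | 1 | 5 × 3.46 / 1 = 17.3 | 100% |
| 5 | 3 | 5 × 3.46 / 3 = 5.8 | 100% |
| 10 | 4 | 10 × 3.46 / 4 = 8.7 | 100% |
| 15 | 4 | 15 × 3.46 / 4 = 13.0 | 100% |

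Rejection is practically certain across this range and carries no information on pain or function.

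**Timing.** The Abstract, the outcome list under Methods and the Number of bands used section all give a count per visit, taken when bands are attached. The analysis section names visits 11 and 12, when none are due. These statements do not fit together.

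**The case against.** The best defence is that the sentence is loosely worded. The reference to visits 11 and 12 closes a list of outcomes, most of which are measured at follow-up, and may date the list as a whole. The Abstract separates the band count, per visit, from the outcomes taken at the two follow-up visits. No section says what is recorded for bands at visits 11 and 12, and the schedule figure is not shown. This stands in part. The zero at visits 11 and 12 is inferred from the treatment schedule, and the failure to estimate belongs to Reading A alone. A reader might infer that the planned model has no variance and cannot be fitted at all. The documents do not support that: the primary method tests change from visit 1, where the intervention arm already has bands, so the model could be fitted and would return a difference by construction. The alternative parsing does not rescue the comparison either, because the band count stays in the list and the control arm stays at zero.

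A second defence is that the count is more than dose delivered, and this stands. A reader might infer that it is purely a measure of exposure and has no place among the outcomes. But the Intervention group section places bands on named acupoints and also on Ashi points, identified by pain or discomfort on pressure. The number may fall as painful points resolve, so its course within the intervention arm may carry some information on response. Only the between-group contrast is at fault.

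The primary null hypothesis speaks of change in each group, which could suggest a within-group test. The Missing data section settles that the MMRM is between groups, and a within-group pre-post test of band count would also lack a pre-treatment value.

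Finally, the practical harm is limited: a model on all zeros fails visibly, and most readers would see why an arm given no bands used none. The article does not say that the band count will support an efficacy claim. This bears on the size of the point, not on its correctness.

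**Conclusion.** The point holds. Applying the primary method to the band count is a stated rule that cannot yield information on benefit: 0 versus 0 and not estimable for raw counts at visits 11 and 12, or a guaranteed difference for change from visit 1 and for counts at visits 1 to 10. The stated timing also needs to be reconciled with the three places that define the count per visit.

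The conclusion rests on the control arm receiving no bands, which is explicit, and on no attachment at visits 11 and 12, which follows from the 10 sessions and from the way visit 11 is dated. The 100% rejection figure rests on the assumed means and SDs. It would change only if very few bands were used or the counts varied far more than assumed, and even then the contrast would only restate the allocation.

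The size is minor: one secondary variable of an exploratory, open-label pilot of 30. The primary outcome, the sample size and the other secondary outcomes are untouched.

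**What to change.** In the analysis section on secondary outcomes, delete the number of bands from the variables analysed by the primary method. Add a sentence that the count will be summarised descriptively in the intervention arm only, per treatment session over visits 1 to 10 (mean, SD, range and course over sessions), with no between-group p value. It may stay in the list of secondary variables if labelled as a descriptive within-arm measure. Align the timing with the per-visit definition in the Abstract, the outcome list and the Number of bands used section.

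The cost is a few words. No new data are needed, since physicians already record the count at each visit, and neither the sample size nor any other analysis changes.

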#### Missing data

This study adopts the MMRM to analyse variations of evaluation parameters for the validity between groups. MMRM considers the missing values by maximum likelihood, not requiring any method of imputing missing values. Conversely, to reduce data loss, the missing values shall be substituted for the Last Observation Carried Forward method in case of adopting the Student paired *t* test (or Wilcoxon signed-rank test) to compare the pre- and post-treatment measurements in groups. Additionally, the Last Observation Carried Forward method shall replace the missing values in case if adopting the repeated measures ANOVA.

### Data handling and safety monitoring

Investigators will collect the data using standard operating procedures with Medidata Rave software (Medidata Solutions Inc., New York, NY, USA). The clinical research coordinator will record all AEs in the study period on the Case Report Form. The investigator will assess the AEs according to patient reports and interviews to verify adverse events, laboratory tests and vital signs. Every severe AE will be reported to the Institutional Review Board and sponsor following Good Clinical Practices and Ministry of Food and Drug Safety regulations. Data and safety reports will be regularly monitored to control the quality of the trial. A clinical research associate will check whether the trial followed the standard operating procedure, study protocol and enforcement rules with source data verification.

## Discussion

When non-invasive treatments fail to adequately treat patients with shoulder pain, shoulder arthroplasty is an essential and effective method to relieve pain and improve shoulder joint function. Minimally invasive arthroscopic shoulder surgery is beneficial for patients who desire less usage of analgesics and earlier return to work [23]. However, postoperative pain is often a concurrent problem that delays rehabilitation and lowers the quality of life [24]. Multimodal pain control, combining pharmaceutical and non-pharmaceutical techniques, is newly recommended to enhance recovery after surgery [25, 26]. Among these techniques, acupoint stimulations, such as acupuncture and electro-acupuncture, are reported as effective to reduce pain and the dosage of narcotics [8].

This study used the Chimsband as an acupoint stimulating method. This medical tape is a combination of adhesive patch, two thin silver lines, and an optic fibre. Chimsband was developed to normalise the bioelectrical current by attaching to the acupoints or on the Ashi points, which are painful areas that usually show abnormally high or low dermal biocurrents. Previous case studies reported their clinical effectiveness in reducing chronic pain and other symptoms from depressive disorders and sleep disorders [13, 16]. However, the mechanism behind the clinical results has not yet been proven in the experimental setting.

This is the first study to evaluate the effect and safety of Chimsband on patients with postoperative shoulder pain. It will utilise the VAS pain scale, SPADI, shoulder ROM, and questionnaires of blood stasis pattern identification as effectiveness parameters.

This clinical trial has several limitations, including its non-blinded design and small sample size; however, it has strength as a preliminary study to assess the potential effectiveness of Chimsband by a randomised controlled trial. Through this study, we expect to generate basic evidence of the effect of Chimsband on controlling pain. Further studies should be conducted with a larger sample size.

## Abbreviations

AE: adverse effect
ICT: interferential current therapy
MMRM: Mixed-effect Model Repeated Measures
ROM: range of motion
SPADI: Shoulder Pain and Disability Index
VAS: visual analogue scale
